In a Canadian study, Stiell, *et al*, employed more rigorous methodology in developing a guideline for imaging of adult blunt trauma patients who have sustained head injuries. This guideline recommends imaging for patients who exhibit any of the following five high risk factors: age 65 years or greater, persistent abnormal GCS scores (<15 for more than 2 hours), suspected open skull fracture, any sign of basal skull fracture, or persistent vomiting (two or more episodes). The criteria in this derivation study identified all cases requiring neurosurgical intervention, but the 95% confidence interval associated with this sensitivity were relatively wide (92 – 100%). This decision instrument also identifies “medium risk factors” (dangerous mechanism of injury, amnesia before impact > 30 minutes) that can be used to identify clinically significant injuries with 98.4% sensitivity (95% CI: 96 – 99%). The authors indicate that their decision rule would have advised imaging in only 54% of their blunt head injury population. However, many of the enrolled patients were followed clinically and never received imaging. The authors do not reveal how many of these patients would require imaging under the decision instrument, nor whether the instrument would actually decrease scanning among patients currently selected for imaging [63].

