While the findings from this study are encouraging, the confidence intervals on the overall sensitivity, and the sensitivity for neurosurgically important lesions are excessively wide. It is likely that application of the decision instrument could readily miss up to 4% of significant intracranial lesions, and up to 8% of neurosurgically important injuries. The decision instrument itself is not applicable to all head injury patients, and contains a substantial list of exclusions, including “minimal head injury” (i.e. no loss of consciousness, amnesia, or disorientation), depressed skull fractures, acute focal neurological deficit, unstable vital signs, seizure, coagulopathy, GCS < 13 on presentation, pregnancy, and age less than 16 years [63]. Furthermore, the study was conducted at ten Canadian academic centers, which limits its external validity and applicability to community hospitals and U.S. practice standards. Finally, the recursive-partitioning scheme used to develop the rule provides an optimal fit only for the data gathered in the study and does not guarantee that the rule will retain its performance when applied to new patients [63]. Before this rule can be used in clinical practice, its performance must be validated in a new cohort of blunt head injury victims. This separate validation study must be conducted in a variety of medical environments and must enroll the large number of cases needed to precisely define the confidence intervals associated its performance.

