Our work also suggests that the relatively small sample size used in the Canadian study may have led to overly optimistic results. In particular, the five “high risk” factors identified by the Canadian study (age 65 years or greater, persistent abnormal GCS scores, suspected open skull fracture, any sign of basal skull fracture, or persistent vomiting), were found in only 869 of the 917 intracranial injury cases identified in our study. This equates to a sensitivity of 94.8% in detecting significant intracranial injury. Fourteen of the missed injury cases required neurosurgical intervention, and provide concrete evidence that the Canadian “high risk” criteria are not 100% sensitive in detecting these important lesions. Errors in the Canadian instrument likely result from the fact that a GCS of 15 is not equivalent to a normal neurological exam. Patients can exhibit subtle neurologic impairments such as altered level of alertness and behavioral abnormalities, and still attain a “normal” GCS score of 15. It is also likely that the additional criteria identified as being important in our work (scalp hematoma and abnormal behavior), are important subtle indicators of intracranial injury that are essential in producing a decision instrument with high sensitivity. Because we did not collect specific information on traumatic amnesia and injury mechanism, we are unable to assess the overall sensitivity of the Canadian instrument, and whether it would decrease imaging among our cohort.

Because of the previously mentioned issues, there is a need for prospective validation of the proposed decision instruments for selective tomographic imaging of blunt trauma victims. We therefore propose an observational study that will document the clinical presentation of blunt head injury victims prior to computed tomographic imaging and combine this observational data with CT results and need for neurosurgical intervention to determine whether combinations of clinical criteria can reliably detect all patients at risk of significant intracranial injuries, reliably exclude injury in low risk patients, and reduce the overall number of CT evaluations in blunt head injury victims.

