In particular, we propose evaluating the performance of a decision instrument composed of the following criteria: 1 - evidence of significant skull fracture, 2 - scalp hematoma, 3 - neurologic deficit, 4 - altered level of alertness, 5 - abnormal behavior, 6 - persistent vomiting, 7 - coagulopathy, and 8 - age greater than 65 years. Furthermore, while it is not the primary goal of this study, we propose a concurrent evaluation of the Canadian decision instrument composed of the following criteria: 1 - age 65 years or greater, 2 - persistent abnormal GCS scores, 3 - suspected open skull fracture, 4 - any sign of basal skull fracture, 5 - persistent vomiting, 6 - dangerous mechanism of injury, 7 - amnesia before impact > 30 minutes. This additional evaluation entails minimal additional burden for the study, and offers the potential to not only validate decision instruments for tomographic imaging, but also enable us to identify the most optimal strategy in terms of reduced CT usage.

Statistically reliable criteria must exhibit a sensitivity quotient of roughly 368/368 to be 95% certain that the true sensitivity is greater than 99.0% (i.e. to validate the sensitivity at the 99.0% confidence level with 95% certainty, the decision instrument would need to identify 368 consecutive intracranial injuries requiring neurosurgical intervention without any misses). The prevalence of neurosurgically important intracranial injuries among blunt trauma victims is between 1.2% and 1.4% [64, 65], which means that approximately 31,000 patients will be needed to guarantee a sample size large enough to provide the necessary statistical significance [48]. Thus, nearly 31,000 blunt head injury victims will be needed to validate the decision instrument for selective tomographic imaging.

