**4.3.7 - Data Analysis**

The primary outcome for the study is the point measure and associated 95% confidence interval for the sensitivity of the decision instrument in identifying patients who require neurosurgical intervention. Additional operator characteristics of interest for this population include the negative predictive value and specificity. Secondary outcomes include the sensitivity, negative predictive value and specificity of the instrument in detecting patients who harbor clinically significant intracranial injuries as described by the criteria defining positive CT imaging (see 4.3.5.1.2 - Injury Diagnosis above). A further secondary goal of the study is to determine and compare the operator characteristics of both the NEXUS head CT instrument, as well as both forms (“high risk” and “medium risk”) of the Canadian head CT instrument, among patients who meet the inclusion and exclusion characteristics for classification by the Canadian rules.

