**EVALUATION**

Please indicate whether any of the following characteristics are present:

Signs of basilar, depressed or diastatic skull fracture: **🞎** Yes **🞎** No **🞎** Unknown

Scalp Hematoma: **🞎** Yes **🞎** No **🞎** Unknown

Neurologic deficit: **🞎** Yes **🞎** No **🞎** Unknown

Abnormal level of alertness: **🞎** Yes **🞎** No **🞎** Unknown

Abnormal behavior: **🞎** Yes **🞎** No **🞎** Unknown

Recurrent or forceful vomiting: **🞎** Yes **🞎** No **🞎** Unknown

Coagulopathy: **🞎** Yes **🞎** No **🞎** Unknown

If yes, check all that apply

Coumadin **🞎** Yes **🞎** No **🞎** Unknown

Aspirin/salicylate **🞎** Yes **🞎** No **🞎** Unknown

Clopidogrel **🞎** Yes **🞎** No **🞎** Unknown

Other (e.g. liver failure, hemophilia, ITP, etc.) **🞎** Yes **🞎** No **🞎** Unknown

Comorbidity (e.g. A-fib, CAD, COPD, Cancer, etc.) **🞎** Yes **🞎** No **🞎** Unknown

Eyes spontaneously open with blinking: **🞎** Yes **🞎** No **🞎** Unknown

Oriented - knows name, age, etc.: **🞎** Yes **🞎** No **🞎** Unknown

Obeys verbal commands: **🞎** Yes **🞎** No **🞎** Unknown

Amnesia > 30 minutes before injury **🞎** Yes **🞎** No **🞎** Unknown

Dangerous mechanism **🞎** Yes **🞎** No **🞎** Unknown

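### The secondary comparison with the Canadian head CT rule cannot be computed as written, because several eligibility and scoring items are not collected

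*Protocol*

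**What the plan says.** Section 4.3.7 makes it a further secondary goal to determine and compare the operating characteristics of NEXUS and of the high-risk and medium-risk forms of the Canadian rule, "among patients who meet the inclusion and exclusion characteristics for classification by the Canadian rules".

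Section 2 describes that rule. Its exclusions cover minimal head injury ("i.e. no loss of consciousness, amnesia, or disorientation), depressed skull fractures, acute focal neurological deficit, unstable vital signs") and continue with "seizure, coagulopathy, GCS < 13 on presentation, pregnancy, and age less than 16 years". Its scoring list has seven items. Besides age, dangerous mechanism and amnesia of more than 30 minutes, it contains "2 - persistent abnormal GCS scores, 3 - suspected open skull fracture, 4 - any sign of basal skull fracture, 5 - persistent vomiting". The GCS item is defined over time: "persistent abnormal GCS scores (<15 for more than 2 hours". Vomiting means two or more episodes.

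Section 4.3.3 lists the data to be collected. It names the NEXUS criteria, the GCS score, dangerous mechanism and amnesia of more than 30 minutes. Appendix B, called a sample form, has date of birth, a stable/unstable flag, one merged skull fracture item, one item for recurrent or forceful vomiting, and three yes/no items related to the GCS, the first being "Eyes spontaneously open with blinking". It has no numeric GCS and no time field.

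**The concern.** Membership of the comparison population and the score of each Canadian form both have to be worked out patient by patient. If the items are not recorded at the bedside, a later analysis plan can only choose proxies; it cannot recover the data.

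The protocol provides no other source. Records are reviewed only for patients with positive CT, and only for neurosurgical intervention (4.2, 4.3.5.1.2). Patients with negative CT, who dominate specificity and negative predictive value, are not reviewed for these items. The link between study number and medical record is later destroyed (4.3.4, 5.2).

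At stake is a named secondary goal. If the gap is found only at analysis, proxies would have to be chosen after the data are in, and some of them shift the Canadian rule's results in a foreseeable direction.

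**Working it through.** The plan states no numerical target for this comparison, so there is no figure to reproduce. The 368 injuries and 31,000 patients belong to the primary outcome. The check matches the Canadian items in section 2 against section 4.3.3 and Appendix B.

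**Selection: nine exclusions**

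| Exclusion | What is recorded | Status |
|---|---|---|
| Minimal head injury | Orientation at assessment; amnesia only if over 30 minutes; no loss of consciousness | Not determinable |
| Depressed fracture | Merged with basilar and diastatic | Not determinable from form |
| Focal deficit | Any neurologic deficit | Proxy |
| Unstable vital signs | Stable/unstable flag | Proxy |
| Seizure | Nothing | Not determinable |
| Coagulopathy | Item present | Captured |
| GCS below 13 | Three yes/no items | Not determinable from form |
| Pregnancy | Nothing | Not determinable |
| Age under 16 | Date of birth | Captured |

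Totals: 2 captured, 2 proxy, 5 not determinable.

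**Scoring: seven items**

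| Item | What is recorded | Status |
|---|---|---|
| Age 65 or more | Date of birth | Captured |
| GCS below 15 beyond 2 hours | One untimed assessment | Not determinable |
| Open fracture | Nothing | Not determinable |
| Basal fracture | Merged with depressed and diastatic | Not determinable when positive |
| Two or more vomits | Recurrent or forceful | Proxy |
| Dangerous mechanism | Item present | Captured |
| Amnesia over 30 minutes | Item present | Captured |

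Totals: 3 captured, 1 proxy, 3 not determinable.

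**Together:** captured 2 + 3 = 5; proxy 2 + 1 = 3; not determinable 5 + 3 = 8; sum 16.

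**GCS below 13 from three yes/no items.** Assumption, not in the protocol: eyes score 1–4, verbal 1–5, motor 1–6, and a yes means the top score for that component.

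| Eyes | Oriented | Obeys | Possible GCS | Below 13? |
|---|---|---|---|---|
| Yes | Yes | Yes | 15 | No |
| Yes | Yes | No | 10–14 | Undecided |
| Yes | No | Yes | 11–14 | Undecided |
| Yes | No | No | 6–13 | Undecided |
| No | Yes | Yes | 12–14 | Undecided |
| No | Yes | No | 7–13 | Undecided |
| No | No | Yes | 8–13 | Undecided |
| No | No | No | 3–12 | Yes |

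Six of eight patterns leave the exclusion undecided.

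**How far other sources help.** If the numeric GCS named in section 4.3.3 is in fact recorded, 8 − 1 = 7 items remain undetermined. Final CT readings are collected on every patient (4.3.5.1.2), and depressed fracture is a listed finding. Recovery is only partial, because that list pairs depressed with diastatic fracture and some closed depressed fractures are classed as not significant. Even if recovery were complete, 7 − 1 = 6 items would remain: minimal head injury, seizure, pregnancy, persistent GCS, open fracture and basal fracture.

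**Direction of the proxies.** A single GCS below 15 generally covers more patients than a GCS that stays below 15 for over 2 hours. The vomiting definition in Appendix C counts a single projectile or forceful episode. Both add Canadian-positive patients, which tends to raise that rule's apparent sensitivity and lower its specificity. The documents do not allow the shift to be sized.

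**The case against.** The strongest reply is that a workable comparison survives and that this is only a further secondary goal. Both medium-risk factors are on the form. Vomiting differs from the Canadian item only for single forceful or projectile episodes. Section 4.3.3 promises a GCS score and Appendix B is only a sample. CT reports help with depressed fracture. Section 2 also reports the five high-risk factors applied to the derivation cohort (869/917 = 94.8%), so the investigators have already used some working definition. Mapping form items to rule items could properly be left to an analysis plan. All of this stands, and it limits the point to the comparison as written.

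It does not remove the point. Section 4.3.3 omits loss of consciousness, shorter amnesia, seizure, pregnancy and open fracture just as the sample form does, and no mapping can supply items that are absent from both.

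Four stronger readings are tempting but unsupported:

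- That most items are missing or that no comparison is possible. Eight of 16 are not determinable from the form; 11 of 16 is reached only by counting proxies as missing.
- That the derivation study failed for the same reason. The statement "we are unable to assess the overall sensitivity of the Canadian instrument" is explained there by missing amnesia and mechanism data, and both are now collected.
- That all 31,000 patients are affected. The comparison concerns only the Canadian-eligible subset.
- That any proxy favours one rule. The two proxies examined trade sensitivity against specificity for the Canadian rule.

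**Conclusion.** The point holds in limited form. The comparison in section 4.3.7 cannot be computed as stated from the data the protocol lists: eligibility for the Canadian rule cannot be established, and neither form can be fully scored as defined. From the form alone 8 of 16 items are not determinable; on the most favourable reading of section 4.3.3 and the CT reports, 6 are, split evenly between selection and scoring. An approximate comparison is feasible and should be labelled as such. The primary outcome, the secondary outcomes on CT-defined injury and the sample size are unaffected.

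This rests on section 4.3.3 and Appendix B together describing what is collected, and, for the GCS patterns, on the component ranges assumed above. Sections 4.3.3 and Appendix B conflict on the GCS score and must be reconciled.

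**What to change.** Before enrolment:

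- Add to Appendix B, and list in section 4.3.3, yes/no/unknown fields for loss of consciousness, any amnesia, post-injury seizure, pregnancy, two or more vomiting episodes, and separate signs of basal, open and depressed fracture (eight fields). Keep the existing merged fracture and vomiting items so that NEXUS scoring does not change.
- Add the numeric GCS at assessment to Appendix B, which reconciles it with section 4.3.3.
- Restate 4.3.7 as a comparison that uses the GCS at assessment in place of the persistent-GCS item, and report it as approximate, with the expected direction of the error. A 2-hour GCS should not be treated as one easily charted value: the protocol does not collect it, and obtaining it for CT-negative patients would mean reviewing charts that are not otherwise opened.

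If the fields are not added, 4.3.7 should describe a proxy comparison and state the mapping of each item.

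Cost: nine more entries per patient, each keyed twice (4.3.6), and in stable patients completed before the CT request is issued (4.3.2.1). The claim for the Canadian comparison becomes slightly weaker. No sample size figure changes.

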**4.3.7.1 - Incomplete Records**

Data from individual study centers will be concatenated into a single database at UCLA. Study records will be reviewed on a twice-monthly basis and regional coordinators informed of missing radiographic reports. The coordinators will be prompted to search for missing cases (as referenced by the study index number). Records of all patients will be reviewed at the close of the study, those lacking tomographic reports will be deleted.

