It is possible that clinicians may not be able to evaluate individual criteria in some patients. For example, it may not be possible to perform a detailed neurological exam and assess motor strength in an individual who has multiple extremity fractures and is unable to cooperate. Clinicians can indicate such occurrences by designating the presence or absence of the individual criterion as “unknown”. The overall decision instrument will treat these “unknown” responses as abnormal responses. Individual risk criteria will be classified as absent only if they can be tested and found to be absent. Consequently, the decision regarding the ultimate need for tomography is based on measuring individual criteria and determining that they are *all absent* in a given individual. If a patient exhibits any of the criteria, or if one or more of the criteria cannot be assessed, the individual will be labeled positive by the decision instrument. Such patients may harbor a significant intracranial injury and should be considered candidates for tomographic scanning. Clinicians are not to use the “unknown” designation in lieu of an adequate evaluation. Our experience with the cervical spine and head injury derivation studies reveals that study physicians use this designation appropriately.

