**4.3.5.1 - Radiographic Imaging**

**4.3.5.1.1 - Radiographic Evaluation**

All patients entered into the main study will initially undergo computed head tomography. Cases will be excluded from the study if the tomography is incomplete and all scan slices are negative. Initial tomography may be supplemented by plain radiographs, additional tomography, angiography or any other imaging study deemed necessary by either ED physicians, neurosurgeons, or radiologists.

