**4.3.7.1.1 - Stable patients**

Because complete survey data will be required on all stable patients prior to computed tomographic requests, these records will only be deleted if radiographic reports and need for neurosurgery are missing.

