**4.3.7.1.2 - Unstable patients**

Unstable patients make up a small minority of minor blunt head injury victims. The exact proportion varies from hospital to hospital. This makes it impossible to accurately estimate how many of these patients may be entered into the study. Because physicians may defer complete data entry on unstable patients, it is possible that final records for some of these patients might be incomplete. However, in our selective cervical spine and previous head injury studies we found that less than 10% of the study patients were classified as unstable, and all of these patients had complete criteria assessments. Thus, missing data from unstable patients is unlikely to be a significant problem in this validation study. In addition, physicians will be required to supply a minimal amount of demographic information on these patients prior to tomographic request generation, and are requested (and required by protocol) to complete data entry on all patients (even though this data entry may be non-concurrent). Records containing incomplete data will not be used in validating the decision instrument. These entries *will* be used in descriptive analyses on the demographics and injuries patterns associated with mild head trauma. Cases missing tomographic reports and information regarding the need for neurosurgical intervention will be deleted from the study.

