**4.3.8.3 - Error Processing and Protection of Data Integrity**

It is possible that a clinician may make an error in a data collection field that is not realized until after the survey has been added to the database. In the event of such an incident, the clinician will be required to submit a corrected survey. The original erroneous survey will remain on the computer database and will not be removed until the data is concatenated into the final data collection. All corrected entries will contain coding information designating the erroneous data they supplant. This strategy will ensure integrity of the database and prevent unauthorized tampering of results. In addition, after final concatenation of survey data and tomography results, the record of any patients who did not have tomographs will be deleted from the study.

As indicated above, data collection may be by-passed on unstable victims. Such cases will be excluded from the study if the data questionnaire is not complete. Clinicians will be informed that an initially incomplete form may be completed at a later time using the same technique as described for error correction. Again, the correct and complete form will contain coded linkages to the incomplete or erroneous data record, and as stated previously all data on physiologically unstable patients will be kept and processed through a separate database. Previous experience has shown that physicians rarely enter incomplete data sets on unstable patients. In our selective cervical spine and head injury studies, we found that physicians were able to complete criteria assessments and record their findings on all unstable patients.

Additional security and data protection will be accomplished through a keyed entry system with entry codes available only to the regional study coordinators and administrators. Individuals who do not have access keys will be able to enter study data using the screen entry program, but will not have access to any additional functions on the computer.

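### The record-deletion rules conflict over a missing CT report and can discard patients whose instrument result or neurosurgical outcome is already known, while the 368-event target has no slack

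*Protocol*

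**What the plan says.** The primary outcome is the sensitivity of the instrument for patients who need neurosurgical intervention (Protocol 4.3.7). Need is defined by death, intubation or a procedure within seven days (4.3.5.1.2). Four sections then decide which scanned patients are kept.

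- **4.3.7.1, all patients:** after a final review of every record, "those lacking tomographic reports will be deleted".
- **4.3.7.1.1, stable patients:** "these records will only be deleted if radiographic reports and need for neurosurgery are missing".
- **4.3.7.1.2, unstable patients:** "Cases missing tomographic reports and information regarding the need for neurosurgical intervention will be deleted from the study". On incomplete forms: "Records containing incomplete data will not be used in validating the decision instrument". The same section keeps those forms for descriptive analyses.
- **4.3.5.1.1, partial scans:** "Cases will be excluded from the study if the tomography is incomplete and all scan slices are negative".

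Two other sections bear on these. Under 4.3.3 a patient who shows any criterion is positive, and "if one or more of the criteria cannot be assessed, the individual will be labeled positive by the decision instrument". Section 4.3.8.3 excludes unstable patients with an unfinished questionnaire from the study altogether, which does not fit their descriptive use in 4.3.7.1.2.

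**The concern.** The primary analysis needs two facts about each scanned patient: the instrument result, and whether intervention was needed within seven days. Several of the rules turn on something else, namely whether a CT report was retrieved, whether a partial scan was positive, or whether every box on the form was filled. A patient can have both facts and still be removed.

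The rules also disagree, so the events counted depend on which sentence the analyst follows, and 4.3.7.1 places the deletion at the close of the study. Hypothesis II in section 1 is that no injury needing neurosurgical intervention is missed, so the handling of a single missed case matters.

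**Working it through.** **1. The rules side by side, for a scanned patient with complete criteria**

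| CT report | Need for neurosurgery | 4.3.7.1 | 4.3.7.1.1 and 4.3.7.1.2 |
| --- | --- | --- | --- |
| missing | missing | delete | delete |
| missing | known | **delete** | **keep** |
| present | known | keep | keep |

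The middle row is the contradiction. It is also a record that the primary analysis could use.

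**2. Partial scans.** Under 4.3.5.1.1 a partial scan with a positive slice stays, and one with only negative slices goes. The later seven-day outcome plays no part. A low-risk patient with a negative partial scan who then needed intervention would be a false negative, and would be removed.

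**3. Incomplete unstable forms.** Under 4.3.3 one criterion recorded as present settles the result as positive, whatever the remaining boxes would show. Section 4.3.7.1.2 nevertheless bars the record from validation. If that patient needed intervention, a true positive is lost.

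**4. The plan's own figure.** Inputs: α = 0.05 used as α/2, target lower limit 0.99, all events detected, prevalence 1.2% (section 3.2). The exact limit is

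P_L = X / [X + (N − X + 1)·F], with F the upper α/2 point on 2(N − X + 1) and 2X degrees of freedom.

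With X = N this reduces to P_L = 0.025^(1/N).

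- N = 368: 0.025^(1/368) = 0.990026. This is the smallest N that reaches 0.99, so the plan's 368 is reproduced.
- Enrolment: 368 / 0.012 = 30,667, consistent with the stated 31,000.

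**5. What a deletion does**

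| Events kept | Misses | Exact lower limit |
| --- | --- | --- |
| 368 | 0 | 0.990026 |
| 367 | 0 | 0.989999 |
| 368 | 1 | 0.98495 |

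Removing one true positive after accrual stops at 368 takes the limit just below 0.99. Removing one false negative turns 367/368 (99.7%) into 367/367 (100%), and the limit rises from 0.98495 to 0.989999. That is still a hair under target; reaching 0.990026 takes one more detected event.

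**6. Range of losses.** The protocol gives no expected number, so these shares are assumptions. With no misses, deleting 1%, 5% or 10% of 368 events leaves 364, 350 or 331, with lower limits of 0.98992, 0.98952 and 0.98892.

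**The case against.** **The conflict has narrow reach, and this largely stands.** Need for neurosurgery is normally abstracted only after a positive CT (4.3.4, 4.3.5.1.2). A patient without a report will therefore usually have no abstracted outcome either, and both rules then delete the record. Coordinators also search for missing reports on a twice-monthly prompt before anything is deleted. Known-outcome, no-report cases arise mainly through the discharge-diagnosis search in 4.3.8.2.

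**Blank forms may be very rare, and this stands.** Sections 4.3.2.1, 4.3.7.1.2 and 4.3.8.3 report complete assessments on all unstable patients in earlier work.

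**The word joining the two conditions may have been meant loosely.** If 4.3.7.1.1 and 4.3.7.1.2 intend deletion when either item is missing, they agree with 4.3.7.1. The plan would then discard known outcomes throughout, so the text still needs correcting.

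Three stronger readings are tempting and not supported:

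- A reader might infer that dropping unstable patients inflates sensitivity. Those with a recorded criterion who needed intervention are true positives. Losing them costs precision and, if anything, lowers the estimate when misses are present. Upward bias needs a deleted false negative.
- A reader might take 4.3.8.3, where "the record of any patients who did not have tomographs will be deleted from the study", as a second statement of the missing-report rule. It concerns patients who were never scanned. That is eligibility for a cohort of imaged patients, not missing data.
- A reader might say that 4.3.3 already requires blanks to be scored positive. Its unknown category is a clinician's entry that an item could not be assessed, and it may not replace an adequate examination. A box never filled in is different, and scoring it positive would push sensitivity upward.

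**Conclusion.** The point holds as a conflict in the text and a poorly chosen criterion for deletion. Section 4.3.7.1 cannot be applied together with 4.3.7.1.1 and 4.3.7.1.2 as worded. Section 4.3.5.1.1 makes retention depend on the scan result, and 4.3.7.1.2 discards some records that are already classified. Sections 4.3.7.1.2 and 4.3.8.3 also disagree on whether incomplete unstable records stay in the study at all.

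The number of records affected is not given and is probably small. The documents do not show that any false negative would be deleted; they show that one could be, for example a low-risk patient with a missing report or a negative partial scan. It matters because the design has no margin: one lost event moves the limit from 0.990026 to 0.989999, and one hidden miss moves it from 0.98495 to 0.989999. Section 4.3.10.3 stops accrual at 368 events without saying whether they are counted before or after deletion, so a shortfall at close is possible but not certain.

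**What to change.** Replace the deletion wording in 4.3.7.1, 4.3.7.1.1 and 4.3.7.1.2, and the exclusion in 4.3.5.1.1, with one rule for patients who were actually scanned:

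- **Primary analysis:** keep a record whenever the instrument result and the need for neurosurgical intervention are both determinable.
- **Look-up before deletion:** before removing a record for a missing or incomplete CT, check the outcome through the existing linkage (4.3.4, 5.2) and the discharge search (4.3.8.2). Under 4.3.4 the linking sheet is cut only after the report and outcome are collected, so it should still be intact for these cases. The check must precede destruction of the sheets and linkage files.
- **Missing or incomplete CT:** this removes a patient only from the CT-based secondary outcomes.
- **Non-events and scope:** CT-negative patients with no intervention found by the existing routes stay as non-events, so specificity and negative predictive value keep their denominators. Never-scanned patients remain outside the main cohort.
- **Incomplete forms:** classify as positive if any criterion is recorded present. A clinician's unknown entry stays positive under 4.3.3. Leave other forms with blanks out of the primary analysis, and report a bounding analysis that counts them as low risk. Align 4.3.8.3 with this.
- **Event count:** state in 4.3.10.3 that the 368 events are counted after these exclusions.

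The cost is protocol wording and an outcome look-up for each scanned record that would otherwise be deleted for a missing or incomplete CT. Accrual lengthens only if events are in fact excluded. For planning, assumed losses of 1%, 2%, 5% or 10% would mean accruing 368/0.99 = 372, 368/0.98 = 376, 368/0.95 = 388 or 368/0.90 = 409 events (rounded up).
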